# Health dialogue intervention versus opportunistic screening in primary care for type 2 diabetes and cardiovascular disease prevention in settings with low socioeconomic status (DETECT): study protocol for a pragmatic cluster-randomized trial

**DOI:** 10.1186/s13063-024-08533-8

**Published:** 2024-10-12

**Keywords:** Screening, Health check, Health promotion, Lifestyle, Prevention, Primary care

## Abstract

**Background:**

Meta-analyses of randomized trials suggest that health checks and health promotion interventions targeting behavior change in primary care do not prevent cardiovascular morbidity and mortality in the general population. However, whether such interventions are more effective in high-risk populations, such as people living in low socioeconomic settings, remains unclear, as they have been poorly represented in previous trials. Therefore, we aim to evaluate the effectiveness, cost-effectiveness, and implementation of systematic screening followed by an individually oriented, lifestyle-focused, health dialogue intervention for prevention of type 2 diabetes and cardiovascular disease, as compared to opportunistic screening, in primary care in socioeconomically disadvantaged areas.

**Methods:**

Using an overall pragmatic approach and a cluster-randomized design with two arms, we aim to enroll 3000 participants aged 50–59 years from 30 primary care centers (PCCs) with an above-average level of Care Need Index in Stockholm Region, Sweden. PCCs will be randomized (1:1) either to a health dialogue intervention, which includes inviting enlisted patients to a systematic screening of risk factors followed by an individually oriented lifestyle-focused health dialogue, or to opportunistic screening, which includes screening patients for a smaller set of risk factors during an appointment at their PCC taking place for other reasons. The main outcome will be change in systolic blood pressure during 6- and 12-month follow-ups. Additional short-term outcomes will be changes in other biological risk factors, health-related quality-of-life, and lifestyle habits, as well as process and implementation outcomes, and unintended side effects. The long-term effect on type 2 diabetes and cardiovascular disease incidence and mortality will be examined using regional and nationwide registers. Changes in systolic blood pressure and other health outcomes will be analyzed using mixed-effect generalized linear modeling and mixed-effect Cox regression to capture variability between and within PCCs. A health economic evaluation will assess resource use and costs in the short- and long-term.

**Discussion:**

This trial of lifestyle-focused health dialogues and opportunistic screening in primary care in socioeconomically disadvantaged areas in the largest region of Sweden has the potential to yield valuable insights that could support evidence-based policymaking.

**Trial registration:**

ClinicalTrials.gov (NCT06067178). Prospectively registered September 27, 2023.

**Supplementary Information:**

The online version contains supplementary material available at 10.1186/s13063-024-08533-8.

## Background

Type 2 diabetes (T2D) and cardiovascular disease (CVD) are estimated to be prevalent in more than 500 and 620 million people respectively, leading to substantial disability, mortality, and economic burden [1–3]. A substantial proportion of the disease burden can be attributed to modifiable risk factors such as hypertension, hyperglycemia, dyslipidemia, obesity, unhealthy diet, smoking, and physical inactivity [1, 4]. Among the indirect favorable consequences of preventive interventions targeting such factors could be a decreased demand imposed on healthcare and welfare systems. Because modifiable risk factors cluster among people with low socioeconomic status [5], targeted interventions may be particularly important to reduce heath inequality.

Primary care has been proposed as a promising arena for the delivery of preventive interventions given its large reach [6]. Some countries, such as Sweden and the UK, have incorporated different types of population-based screening programs and health assessments into primary care [7, 8]. Unfortunately, the scientific evidence supporting large-scale implementation of such programs is weak, as reported by numerous Cochrane meta-analyses of randomized trials. One meta-analysis found limited evidence that systematic screening (predetermined and systematic process for selecting and inviting participants to a screening program) compared to opportunistic screening (sporadically occurring risk assessment without systematic invitation) can have favorable effects on some risk factors such as blood pressure but not on cardiovascular events [9]. Similarly, another meta-analysis concluded that systematically offered general health checks have no effects on cardiovascular events as compared to no health checks [10]. Both of these meta-analyses focused on trials in healthy adults from the general population, making generalizability to high-risk populations uncertain.

Another possibility is that screening alone might not be sufficient to induce improvements in risk factors, thereby limiting its ability to subsequently reduce clinical outcomes, which would suggest the need for more intense interventions. For example, one meta-analysis of health promotion interventions aimed at behavior change found that although such interventions do not reduce cardiovascular events in general populations, they might be effective in certain risk groups, i.e., people with hypertension and T2D [11]. Similarly, another meta-analysis of health promotion interventions targeting risk groups, in this case people living in low- and middle-income settings, suggested beneficial effects on some surrogate measures such as blood pressure. Yet, heterogeneity was substantial and there was not enough evidence to determine the effect on cardiovascular events and lifestyle habits [12], lending the authors to request further trials.

In Sweden, a prevention program has been developed in primary care since the mid-1980s [13, 14]. The program includes systematic screening of T2D and CVD risk factors followed by a person-centered lifestyle health dialogue based on the individual risk profile. The screening assessment includes questionnaires assessing a wide range of factors including medical history, medications, general health, mental health, heredity, living situation, quality-of-life, and lifestyle habits as well as blood tests of biological risk factors, blood pressure measurement, and anthropometric measurements. A recent systematic review suggested that the Swedish prevention program reduces all-cause mortality, cardiovascular mortality, blood pressure, cholesterol, blood glucose, waist circumference, and body mass index, while positively influencing dietary habits [15]. No effects of the program were detected for physical activity, tobacco use, and alcohol consumption. It should, however, be noted that the quality of the underlying evidence ranged from low-to-moderate, and six out of seven studies included in the review were observational. Moreover, the Swedish program has neither been implemented or evaluated in settings specifically targeting socioeconomically disadvantaged settings nor has it been compared to other preventive interventions. This would be important given the typically lower participation rates observed in these areas [16].

Based on the available evidence outlined above, it could be hypothesized that an intervention acting on the results of a screening assessment, i.e., person-centered lifestyle health dialogues, might be beneficial if it targets specific populations with a high burden of risk factors such as people in low-socioeconomic settings, rather than the general population. Targeting risk groups instead of a whole population may not only be more effective and cost-effective [17] but can also be important for tackling health inequalities. Considering the scarcity of evidence regarding the effectiveness, cost-effectiveness, and implementation of such preventive efforts delivered in primary care in areas with low socioeconomic status, a trial addressing this knowledge gap has the potential to contribute to the evidence base of these forms of interventions.

### Objectives

The overall aim of the *Health Dialogue intErvention versus opporTunistic scrEening in primary Care for Type 2 diabetes and cardiovascular disease prevention in settings with low socioeconomic status* (DETECT) trial is to evaluate the effectiveness, cost-effectiveness, and implementation of a systematic screening followed by an individually oriented, lifestyle-focused, health dialogue intervention (HDI) for prevention of T2D and CVD, as compared to opportunistic screening (OS), delivered in primary care in socioeconomically disadvantaged areas in Stockholm, Sweden. The primary outcome is change in systolic blood pressure, which is used as a surrogate outcome for the target outcome of CVD incidence. In 2022, there was a formal political decision that the Swedish prevention program for lifestyle-focused health dialogues should be implemented in primary care across the Stockholm Region as a pilot program. Consequently, the Health and Medical Care Administration commissioned Centre for Epidemiology and Community Medicine, and Academic Primary Health Care Centre, to implement and conduct an evaluation of the health dialogue pilot program. The original plan for the pilot program included a third arm receiving usual care. Unfortunately, due to limited initial responsiveness from primary care centers (PCCs), the trial could not be powered for a three-arm comparison. As a result, priority was given to comparing the two interventions described below.

The specific aims of this trial are to evaluate the following: (I) the long-term effects on T2D and CVD incidence and mortality among participants receiving HDI as compared to participants receiving OS; (II) the short-term effects on biological risk factors (blood pressure, cholesterol levels, glucose levels, body mass index) and health-related quality-of-life (HRQoL), among participants receiving HDI as compared to participants receiving OS; (III) the short-term effects on lifestyle habits (tobacco/nicotine usage, dietary habits, alcohol consumption, physical activity), among participants receiving HDI as compared to participants receiving OS; (IV) the potential effect modification by sex, socioeconomic status, and birth country, for all of the above; (V) the differences in resource use and associated costs between HDI and OS in the short and long terms; (VI) the costs per quality-adjusted life year (QALY) and per blood pressure target attained associated with HDI as compared to OS in the short term; and (VII) the cost per life year gained associated with HDI as compared to OS in the long-term.

Additionally, we will assess various implementation and process outcomes, including (I) the number of invited PCCs that agree to participate; (II) the adherence to the original intervention protocols by healthcare professionals; (III) the perceived acceptability, appropriateness, and feasibility of implementing the interventions among healthcare professionals; (IV) the barriers and facilitators for implementation of the interventions among healthcare professionals; (V) the proportion of patients choosing to participate among those invited and the reasons for declining participation among non-participants; (VI) the representativeness of participants as compared to the total eligible population based on socioeconomic characteristics; (VII) the case-finding rates, defined as the proportion of participants among whom elevated levels of biological risk factors are detected for the first time; and (VIII) the estimated time needed to treat (TNT).

## Methods

### Study design and setting

This is a pragmatic, population-based, superiority, cluster-randomized trial with two intervention arms, of which one serves as comparator. The first arm (HDI) consists of a systematic screening followed by an individually oriented lifestyle-focused health dialogue based on the risk profile obtained from the screening. The second arm (OS) consists of opportunistic screening and represents the comparator. The PCCs represent the clusters and unit of randomization, while patients and healthcare professionals at the PCCs represent units of observation.

This trial will be conducted within primary health care in the Stockholm Region in Sweden. The Stockholm Region has the largest population of the 21 regions in Sweden. The region had a total of 2,440,027 (23.2%) inhabitants in 2022, of which 313,924 were aged 50–59 years old, according to official, publicly available data from Statistics Sweden. In Sweden, primary care is part of the tax-funded health system, which is governed and managed by the 21 regions, which includes both public and private PCCs. In 2022, there were a total of 231 PCCs in Stockholm Region, of which 67 were public and 164 were private. The public and private PCCs are funded and governed according to the same rules but differ in how they are organized and managed. Both public and private PCCs will be included in this trial. The target population is individuals living in areas of low socioeconomic status, and we will therefore select PCCs based on their Care Need Index (CNI). The CNI is a social deprivation index which describes the expected risk of ill health within a patient population, based on socioeconomic and demographic factors [18].

### Trial reporting and ethical approval

Reporting of this protocol is guided by the Standard Protocol Items: Recommendations for Interventional Trials (SPIRIT)-Surrogate extension guidelines [19]. The results will be reported according to the Consolidated Standards of Reporting Trials (CONSORT) guidelines, with extensions to surrogate endpoints and cluster trials [20, 21]. Ethical approval of the trial has been granted by the Swedish Ethical Review Authority (Dnr. 2023–03001-01). The trial has been pre-registered at https://clinicaltrials.gov with reference number NCT06067178, where all items from the World Health Organization Trial Registration Data Set are available. Any major modifications of the protocol will be communicated to the trial registry.

### Sample size

Sample size calculations were based on change in systolic blood pressure as the main outcome measure. We considered a 5-mmHg reduction in systolic blood to be clinically relevant as meta-analyses of randomized trials show that such a reduction can reduce the risk of CVD by about 10% regardless of CVD history, including among people with normal to high-normal blood pressure [22], as well as specifically in middle-aged adults [23].

Based on systolic blood pressure data in Stockholm Region that were obtained from electronic medical records, the estimated variance of systolic blood pressure levels between PCCs (clusters) was equal to 2, and the variance between subjects within PCCs (individuals) was equal to 256. These settings give rise to the underlying variance structure of the data, essential for sample sizes calculations, namely a difference of 5 mmHg in systolic blood pressure between arms (VA = 12.5), variance between clusters, (VC = 2), and variance between individuals within PCCs (VE = 256). We calculated the number of clusters, the number of individuals, and the power of the sample using various combinations of VA, VC, and VE values close to those outlined above. For each calculation, we adjusted one parameter while holding the other two constant. We used the package clusterPower version 0.7.0 [24], R Statistical Software version 4.1.3 [25], for the sample size and/or power calculations for the different variance settings.

Accordingly, we calculated that based on 15 clusters in each arm, a minimum of 840 participants (*n* = 420 in each arm and *n* = 28 per cluster) would yield 80% power to detect a reduction of 5 mmHg systolic blood pressure in the HDI group as compared to OS. Rising power to 90% while keeping the number of clusters to 15 per arm would require a minimum of 1200 participants (*n* = 600 in each arm and *n* = 40 per cluster). Additionally, anticipating difficulties with cluster recruitment and retention, we also calculated that if the size of the cluster is increased to *n* = 69, a power of 80% would be obtained with 9 clusters per arm, and 90% power would be obtained with 11 clusters per arm. Because we expected difficulties with recruitment of PCCs and participant recruitment within PCCs, as well as subsequent attrition of the two, the goal was to recruit at least 30 PCCs (*n* = 15 in each arm) in Stockholm Region, each of which will aim to recruit *n* = 100 participants, yielding a maximum total study population of *N* = 3000.

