This trial will have limitations that should be considered. First, although the pilot program underlying this trial employs an overall pragmatic approach, certain measures had to be taken that may interfere with what would be considered pragmatic. For instance, some implementation strategies had to be applied. This was deemed necessary given that even though health dialogues are used across many regions in Sweden, and opportunistic screening may be used occasionally, neither of these are part of the systematic core activities of Swedish primary care. As such, we believe that implementation strategies must also be considered in any future scale-up of the interventions in clinical practice. Second, we acknowledge a risk of selection bias due to post-randomization recruitment of participants that are not blinded to treatment allocation [52]. Various mitigation strategies have been proposed to reduce this bias, such as using blinded independent recruiters and providing both arms with similar trial information and consent forms [52]. While unable to use a blinded independent recruiter in our trial, we kept trial information and consent forms similar for HDI and OS. This information is published together with this protocol, to increase transparency and aid in interpretation of trial results [52]. Nevertheless, some bias will likely remain, which could affect (in an unpredictable direction) the internal validity of the head-to-head comparison of the two interventions. Consequently, to tackle imbalances in characteristics (at both cluster and individual level) between arms, the analyses will employ covariate adjustment, which has been deemed particularly important in trials where participants are unblinded and recruited post-randomization [52]. Third, this trial will not include a care as usual care-arm. If one would assume that OS may be more effective than usual care, while recognizing that OS is the comparator in this trial, this could in theory mean that any potential benefits from HDI may become masked due to insufficient exposure contrast. However, a previous meta-analysis found that compared to OS, even systematic screening interventions of lower intensity than our HDI intervention may have favorable effects on some risk factors, including a 3-mmHg reduction in systolic blood pressure [9]. Moreover, a head-to-head comparison of HDI and OS will be relevant for clinical practice given that OS is an approach that is sometimes used by clinicians, although not systematically. Fourth, we made several sample size calculations with varying assumptions to ensure sufficient statistical power under different scenarios that may occur due to attrition. Although these calculations suggested that we should have sufficient statistical power even with many dropouts, unexpected situations may emerge that are beyond our control. For example, PCCs facing high staff turnover and/or saving requirements could be reorganized and shift resources towards core activities, away from trial participation.

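### The stated sample sizes and powers do not belong to a 5 mmHg difference; with the protocol's own variances they fit about 3.54 mmHg, the square root of VA = 12.5

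*Protocol article*

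**What the plan says.** The Sample size section sets the inputs as "a difference of 5 mmHg in systolic blood pressure between arms (VA = 12.5), variance between clusters, (VC = 2") with a variance of 256 between individuals within PCCs. Both variances are presented as estimates from the region's own patient data. For the clusters, the text reads "the estimated variance of systolic blood pressure levels between PCCs (clusters) was equal to 2".

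Four results follow:

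- For 840 participants (15 clusters per arm, 28 in each), the claim is that this size "would yield 80% power to detect a reduction of 5 mmHg systolic blood pressure in the HDI group as compared to OS".
- With 15 clusters per arm and 40 per cluster (1200 participants), the power is 90%.
- With 69 per cluster, "a power of 80% would be obtained with 9 clusters per arm, and 90% power would be obtained with 11 clusters per arm".

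The recruitment goal is 15 PCCs per arm with 100 participants each, 3000 in all. The Discussion leans on this work when it says that "these calculations suggested that we should have sufficient statistical power even with many dropouts". It also cites a meta-analysis in which systematic screening lowered systolic pressure by 3 mmHg compared with opportunistic screening.

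**The concern.** A 5 mmHg difference against a within-cluster SD of 16 (the square root of 256) and an ICC of 2/258 = 0.008 is easy to detect with 840 people in 30 clusters. A stated power of only 80% looks too low. The entry VA = 12.5 suggests a reason: it equals 5²/2, the variance of two arm means 5 mmHg apart, and it is not the squared difference, which is 25.

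The power statement is what readers will use to judge a result below 5 mmHg. As printed, it implies that about 840 participants are needed to see 5 mmHg, and it gives no detectable difference for the planned 3000. The protocol itself names 3 mmHg as an effect already seen for a similar contrast, so the detectable difference matters. The 9- and 11-cluster scenarios, meant for the case where PCCs are lost, carry the same mismatch.

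**Working it through.** **Inputs.** Difference d = 5 mmHg, VC = 2, VE = 256, and the four combinations of k clusters per arm and m per cluster, all from the Sample size section. Alpha is not stated; two-sided 0.05 is assumed.

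**Formula.** SE = √[2(VC + VE/m)/k]. Power comes from the noncentral t distribution with 2(k − 1) df and noncentrality d/SE.

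**One case in full (k = 15, m = 28).** VC + VE/m = 2 + 256/28 = 11.143. SE = √(2 × 11.143/15) = 1.219. The critical t on 28 df is 2.048.

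- d = 5: noncentrality 5/1.219 = 4.10, power 97.7%.
- d = √12.5 = 3.536: noncentrality 3.536/1.219 = 2.90, power 79.95%.

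**All four scenarios.**

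| Clusters per arm × size | Stated power | SE | Power at 5 mmHg | Power at 3.54 mmHg | Difference detectable at the stated power |
|---|---|---|---|---|---|
| 15 × 28 | 80% | 1.219 | 97.7% | 79.95% | 3.54 mmHg |
| 15 × 40 | 90% | 1.058 | 99.5% | 89.7% | 3.56 mmHg |
| 9 × 69 | 80% | 1.127 | 98.6% | 83.8% | 3.36 mmHg |
| 11 × 69 | 90% | 1.019 | 99.7% | 91.0% | 3.47 mmHg |

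The last two rows overshoot at 3.54 mmHg because clusters come in whole numbers. Eight clusters of 69 give 78.6% and nine give 83.8%; ten give 87.9% and eleven give 91.0%. So 9 and 11 are the smallest numbers reaching 80% and 90% at 3.54 mmHg.

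**Sizes that 5 mmHg needs.**

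- 15 clusters per arm, 80% power: 13 per cluster (81.0%; 12 give 78.1%), so 2 × 15 × 13 = 390. The stated minimum is 840, and 840/390 = 2.15.
- 15 clusters per arm, 90% power: 18 per cluster (90.7%; 17 give 89.3%), so 2 × 15 × 18 = 540. The stated minimum is 1200, and 1200/540 = 2.22.
- 69 per cluster: 5 clusters per arm for 80% (82.5%) and 6 for 90% (90.3%), against the stated 9 and 11.

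**Planned size, 15 × 100 per arm.** SE = √[2(2 + 2.56)/15] = 0.780. The detectable difference is 2.26 mmHg (80%) or 2.62 mmHg (90%), and power for 3 mmHg is 96%.

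**Can another reading rescue 5 mmHg?** Powers are in the order of the table.

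- Normal approximation: 98.4, 99.7, 99.3 and 99.8%. A one-sided test raises power further.
- Using k − 1 df, as for matched pairs: between 96.8% and 99.3%.
- Alpha 0.01: 90.0, 96.9, 91.8 and 97.2%. Alpha 0.001: 66.1, 83.5, 65.6 and 82.8%. Neither gives 80/90/80/90.
- Changing VC alone: it would have to be 13.1, 10.2, 8.9 and 8.1 in the four scenarios, against a stated 2.
- Changing VE alone: 567, 585, 733 and 678, against a stated 256.

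**The case against.** The mismatch cannot be argued away, but its cause can be disputed. Power depends on d² relative to the variances, so halving d² (25 to 12.5) has the same effect as doubling both variances. With VC = 4, VE = 512 and d = 5 mmHg, all four powers come out the same: 79.95, 89.7, 83.8 and 91.0%. There is even a motive, since the outcome is a change in pressure while the variances describe levels, and the difference of two uncorrelated measurements has twice the variance. If that was done, 5 mmHg is the right label and the printed variances are wrong. The planned 15 × 100 would then detect 3.20 mmHg (80%) or 3.70 mmHg (90%), with about 75% power for 3 mmHg.

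This does not save the text. The doubled values are not printed, and the section says that only one parameter was varied at a time, to values near the stated ones. It does mean that the mechanism is an inference.

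Two further points stand. The close match to 3.54 mmHg depends on a two-sided 5% t calculation; a normal approximation puts the 15-cluster scenarios at about 3.42 to 3.43 mmHg. And on the printed inputs the error is on the safe side: the Discussion's claim of adequate power under dropout remains true for 5 mmHg, with more margin than the stated figures suggest.

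**Conclusion.** The concern holds. On the protocol's printed variances, none of the four power figures is right for 5 mmHg: actual power is 97.7% to 99.7% where 80% or 90% is stated, and the stated minimum sizes are about 2.2 times what 5 mmHg requires. Read with those variances, the stated designs are designs for about 3.5 mmHg. This assumes a two-sided 5% test, but no test convention tried makes 5 mmHg fit. That the square root of 12.5 served as the difference is the likeliest explanation consistent with the printed inputs, but it is not proven.

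The trial is not underpowered for 5 mmHg on its own inputs, and nothing in its conduct is affected. What is wrong is the published power statement, and with it the basis for interpreting an effect below 5 mmHg or the loss of PCCs. It should be corrected.

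**What to change.** Look up the values entered in the original R run, then correct the paragraph. With the printed variances there are two consistent ways to do so:

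1. Keep 840 and 1200 participants and the 9- and 11-cluster scenarios, and say that they detect about 3.5 mmHg.
2. Keep 5 mmHg and give the matching sizes: 13 and 18 per cluster with 15 clusters per arm, and 5 and 6 clusters per arm with 69 per cluster.

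If the run shows that larger variances were used, print and justify those instead. In every case state alpha and sidedness, and add the detectable difference for the planned 3000 (2.26 mmHg at 80% and 2.62 mmHg at 90% with VC = 2 and VE = 256).

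The cost is one rerun of the code and one corrected paragraph. Recruitment targets and the trial's size stay as they are.
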